## Objectives

### Phase 1 objectives

a. To compare healthcare professionals’ perceptions of their **capacity, capability and confidence** to deliver safe, holistic, individualised cancer care to children and young people with and without learning disabilities and/or autism

*We hypothesise that health professionals will perceive that they have less capacity, capability and confidence to deliver safe, holistic, individualised cancer care to those with learning disabilities and/or who are autistic and their families, compared to those without.*

b. To compare patient demographics, **care trajectory, symptom profiles and clinical** outcomes related to cancer care for children and young people with and without learning disabilities and/or autism

*We hypothesise that* c*hildren with learning disabilities and/or who are autistic*

- *will have a longer length of stay compared to children without learning disabilities and/or who are autistic and their families*- *will have increased number and severity of side effects compared to children without learning disabilities and/or who are autistic and their families*

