### Retrospective clinical case note review (1c)

The research team will work with the local digital data team to a) define the cohort specification, b) extract data according to pre-defined criteria such as patient demographics, co-morbidities, care episodes (e.g., length of stay, unplanned admissions), symptom profiles and treatment toxicity (e.g., pain, constipation, nausea and vomiting), and clinical outcomes (e.g., mortality, requirement for a bone marrow transplant, transfer to an end-of-life pathway).

The inclusion criteria will encompass children and young people who have received cancer care at the primary hospital research site between 1^st^ April 2019–31^st^ December 2023. This timeframe accounts for the implementation date of a new electronic patient record system within the hospital to the current time. A subsequent process will be undertaken to determine which of these patients have diagnoses of learning disabilities and/or ASD compared to those without. Within the digital environment, ICD-10 cancer related terms in oncology and haematology will be applied to establish the total case number. Against this case list, phrases relating to learning disabilities and ASD diagnoses will be applied to distinguish those cases with cancer and diagnoses of learning disabilities and/or ASD and those without. Data will be deidentified prior to analysis by the research team.

Data will cover standard structured clinical administrative data and free text clinical notes for all patients from the Electronic Patient Record (EPR) system. A data analyst will use Python and R to develop the pre-processing and exploratory data analysis code required in the initial pilot phase of the study. This analyst will develop a pipeline to wrangle the data into a format that is suitable for downstream analysis, including implementation of a text mining/search process and rule-based algorithm to identify and classify patients with and without learning disabilities and/or ASD diagnoses.

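### The case note review does not fix when a learning disability or ASD diagnosis must be recorded relative to cancer diagnosis, so the group label can depend on the outcomes being compared

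*Protocol article*

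**What the plan says.** All of this is in the Protocol article, mainly under Retrospective clinical case note review (1c).

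- **Entry.** The cohort is "children and young people who have received cancer care at the primary hospital research site" between 1 April 2019 and 31 December 2023. Entry is by receipt of care, not by a new cancer diagnosis in the window.
- **Grouping.** The split comes after the cohort is formed: "A subsequent process will be undertaken to determine which of these patients have diagnoses of learning disabilities and/or ASD compared to those without". Against the cancer case list, "phrases relating to learning disabilities and ASD diagnoses will be applied to distinguish those cases with cancer" and a diagnosis of either kind from those without. The means is a "text mining/search process and rule-based algorithm to identify and classify patients with and without learning disabilities and/or ASD diagnoses", still to be developed.
- **Source.** The extract is "standard structured clinical administrative data and free text clinical notes for all patients from the Electronic Patient Record (EPR) system".
- **Outcomes.** The same extraction supplies "care episodes (e.g., length of stay, unplanned admissions), symptom profiles and treatment toxicity", together with mortality and other clinical outcomes.
- **Hypotheses.** Phase 1 objectives state that the learning disability/autism group "will have a longer length of stay compared to children without learning disabilities", and that it will have more, and more severe, side effects.
- **Bias control.** The analysis paragraph that follows names propensity score matching, where appropriate, on factors it does not list. It treats differences in the matched cohorts as the real ones.

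**The concern.** Exposure and outcome are read from one record, and no baseline date separates them. That opens three routes by which the outcome, or its cause, could shape the label.

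1. **Record length.** More inpatient days produce more notes, and so more chances that a qualifying phrase appears.
2. **Acquired impairment.** A child whose learning difficulty follows from a brain tumour or its treatment could enter the exposed group because of the heavy treatment whose burden is being compared.
3. **Short follow-up.** A child who dies early, or is very young, has less opportunity to be labelled and could fall into the comparator group.

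The first route pushes stay and side effects in the hypothesised direction. The third tends to flatter mortality in the exposed group. At stake is whether a positive result could be told apart from a labelling artefact.

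**Working it through.** The case note review gives no sample size, prevalence, effect size or search accuracy, so there is no stated figure to reproduce. What follows is illustration. Every input is an assumption unless a source is named.

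**1. Record length, no true effect.** Assume 6% truly have learning disability/ASD (π = 0.06). Total inpatient days d are log-normal with median 30 and log-SD 1, identical in both groups. A share k is already documented at baseline, and the rest are picked up at rate h per inpatient day:

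P(flag | d) = k + (1 − k)(1 − exp(−h·d))

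Mean days, flagged = E[d·P] / E[P]

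Mean days, unflagged = (E[d] − π·E[d·P]) / (1 − π·E[P])

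Here E[d] = 30 × exp(0.5) = 49.46. Worked case, k = 0.5 and h = 0.01: E[P] = 0.659 and the flagged mean is 58.71, so E[d·P] = 0.659 × 58.71 = 38.69. The unflagged mean is (49.46 − 0.06 × 38.69) / (1 − 0.06 × 0.659) = 49.08. The ratio is 58.71 / 49.08 = 1.20, where the truth is 1.00.

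| Documented at baseline (k) | h = 0.005 | h = 0.01 | h = 0.02 |
|---|---|---|---|
| 70% | 1.08 | 1.10 | 1.10 |
| 50% | 1.17 | 1.20 | 1.18 |
| 30% | 1.33 | 1.34 | 1.29 |

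These are by numerical integration. Simulating the same model gave 9–11%, 18–21% and 30–35% for the three rows, which is close agreement. If only the baseline-documented share is labelled (h = 0), the ratio is 1.00.

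**2. Would this yield a false positive?** The Setting section gives about 500 patients a year. The window is 4.75 years, so 500 × 4.75 = 2,375 is an upper bound that ignores patients seen in more than one year. Testing log-days with 1:1 random controls (4,000 runs per cell), a significant result in the hypothesised direction arose in 6–11% of runs (k = 70%), 14–26% (50%) and 29–52% (30%), against a nominal 2.5%.

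**3. Share of acquired cases.** Acquired share = (CNS share × acquired risk) / (CNS share × acquired risk + pre-existing prevalence). Low end: 0.20 × 0.05 / (0.20 × 0.05 + 0.05) = 16.7%. High end: 0.25 × 0.20 / (0.25 × 0.20 + 0.03) = 62.5%.

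**4. Direction, under a second set of assumptions.** Prevalence is 8%, with the same distribution of days. Entries are geometric mean ratios of stay, labelled against unlabelled.

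| Scenario | True ratio | Observed |
|---|---|---|
| Detection rises with days, no false hits | 1.0 | 1.20 |
| Same, plus false hits at 0.05% per day | 1.0 | 1.53 |
| Same, plus false hits at 0.1% per day | 1.0 | 1.74 |
| Acquired cases, subgroup stay × 1.5 | 1.0 | 1.10 |
| Acquired cases, subgroup stay × 1.0 | 1.3 | 1.20 |
| Acquired cases, subgroup stay × 0.7 | 1.3 | 1.10 |
| Label errors unrelated to stay (sensitivity 0.8, false positives 3%) | 1.3 | 1.20 |

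Detection and false hits that accrue with record length inflate the contrast. The last three rows attenuate a real difference. A label limited to pre-cancer records gave 1.00 when the truth was 1.0 and 1.28–1.30 when it was 1.3.

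**The case against.** The strongest reply is that this is a condensed article. The cohort specification is still to be agreed with the digital data team, the algorithm is not yet built, and terminology is left to a supporting file that is not shown. The target is diagnoses rather than any mention, and structured data are used as well as free text. A reader might infer that any phrase, anywhere in the record and at any time, will count. The article does not say so, and that reading should not be attributed to it.

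Other parts of the reply also carry weight. The matching factors are open: age, tumour type or treatment could be among them and would ease the second and third routes. The Aim runs through to survivorship, so acquired disability may be a legitimate interest. Total inpatient days is only one reading of length of stay. If stay is analysed per episode, the link to record length may be weaker. Outpatient notes and referral letters would also weaken it.

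What remains is that the article does set out the sequence: cohort by receipt of care, then phrase search, then matching, then a claim to real differences. A baseline date is absent from that sequence. Matching on covariates cannot undo a label that depends on the outcome. Interest in acquired disability is a reason to report those children separately, not to pool them.

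**Conclusion.** The point holds as an unfixed timing rule with a plausible and partly predictable bias. As described, outcome-dependent labelling and treatment-acquired exposure are not excluded. Stay and side-effect contrasts could be inflated, and mortality could be biased in the exposed group's favour.

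The size in this study cannot be computed from the document. The 8–34% figure for falsely longer mean stay rests on the assumed prevalence, stay distribution, baseline documentation and pick-up rate.

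A reader might go further and conclude that the hypotheses would be confirmed even with no true difference. That is not supported. In nearly all the no-effect scenarios a false positive was the less frequent result, although well above the nominal rate. Acquired cases without longer stays, and label errors unrelated to stay, pull towards no difference.

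**What to change.** Write the timing rule into the cohort specification before the algorithm is built.

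- **Baseline.** In the primary comparison, count a child as learning disability/ASD only if the diagnosis is coded, or documented as pre-existing, at a fixed baseline, for example the referral or a short window after the first cancer encounter. Count congenital or genetic causes, such as Down's Syndrome, whenever recorded.
- **Earlier cancers.** For children whose cancer was diagnosed before April 2019, either apply a stated rule (for example, a note documents that the diagnosis pre-dated the cancer) or limit the primary comparison to children newly diagnosed within the window.
- **Search rules.** Exclude negated, queried and family-history mentions.
- **Matching.** Include age band among the matching factors.
- **Later cases.** Report later-recorded or acquired cases as a separate group in a sensitivity analysis.

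The cost is a somewhat smaller exposed group, and so some loss of precision, plus a little more extraction work: a date for each qualifying entry and the added rules.

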### Phase 2 qualitative

#### Ethnography (2a).

As is typical with Ethnographic studies, a purposeful sampling strategy will be used [40] to select participants according to pre-determined criteria. The sample size will be reflective of the expected time needed to build relationships with children with learning disabilities and engage them in the research process, as well as the knowledge that Ethnographic research yields large amounts of data. Early data analysis will iteratively inform further sampling to expand, refine and exhaust thematic development [43]. In this study, recruitment to data saturation will mean the corpus of data will be “large enough to capture a range of experiences but not so large as to be repetitious” ([44], p.193). Therefore, we will ensure that the full scope of the topic is explored in sufficient depth. We aim to recruit approximately 25 families with a ratio of 2:1 children with learning disabilities/ASD compared to those without.

The inclusion and exclusion criteria are outlined in Table 1.

**Table 1 pone.0333020.t001:** Eligibility criteria of participants for phase 2 data collection.

Participant	Inclusion criteria	Exclusion criteria
Children and young people	Receiving cancer care at the hospital research site, with/without learning disability, and/or who are autistic Ages 5–15	Within palliative care at the time of recruitment Subject to child safeguarding proceedings Outside of stated age range Where the family would prefer to maintain a complete non-disclosure approach to their child’s cancer diagnosis and feel their child’s participation may infringe on this request
Parents	Of children receiving cancer care in hospital research site If included for interview only, child’s age may be 0–15	Has mental health difficulties that would impair ability to participate effectively or create an unmanageable risk, e.g., psychosis

Data collection will include observations of the patient’s journey, clinical encounters, key ward events and key meetings between health professionals. Observation will be fully overt, with a visible encrypted digital recorder used to record conversations and written ethnographic fieldnotes will be kept [39]. Key recordings will be used to support more rapid write up of field notes and will be transcribed verbatim, providing an opportunity for conversation analysis [45].

Data collection will include informal discussions/creative sessions with children and parents. To ensure the research process is meaningful for children, irrespective of their communicative or intellectual ability, a toolkit of creative techniques suitable for children with learning disabilities and/or who are autistic will be available in line with the Mosaic Approach to research [46]. This could include resources such as Talking Mats, recordable speech bubbles, photography, objects of reference or play. Furthermore, a data collection research activity journal has been co-designed in conjunction with children, families and illustrators. The journal includes accessible and child appropriate activities for completion in between and during observations. The book is customisable with a mix of other fun activities such as writing, drawing and puzzles. Children will be able to complete as many or as few of the activities as they would like. The content of these entries will be revisited by the researcher with the children and young people and their parents to explore things that are meaningful to them, including about their identity, experience and reflections. We aim to understand aspects of children’s and young people’s multisensory experience within the ethnography [47,48]. Photography will be used by both children and young people and the researcher to capture important visual data relevant to the study aims [49]. Children and young people will use an instant camera to develop photographs that they will be able to stick into their activity book. Most important in the data collection process is being non-prescriptive and drawing on methods in accordance with children’s strengths and preferences, thereby enabling them to share their story in whatever way they are able and feel comfortable doing [50].

Families will be able to choose to participate in the ethnography to whatever level of involvement they prefer; for example, ranging from one-off 1−1 interviews to full involvement with observation and creative interviews. Our advisory groups have highlighted that siblings should not be overlooked and so they will be invited to participate where it is relevant to the study aims. In the circumstance that a child is isolated due to infection control precautions we will still offer the family the opportunity to participate. Where it is viable, discussions will take place between the researcher and the family via video conference calls and the child’s access to the creative resources/methods will be facilitated with the support of parents.

Phase 2 ethnography will include collection and analysis of material artifacts, such as a hospital passport or care plans, which will be explored for relevant information relating to the child’s strengths and needs in relation to their clinical care, with photos taken of these to illustrate findings. Documentary evidence will also involve access within the hospital electronic patient record for data extraction. Only data that are relevant to the study aims will be sought and accessed, for example the details of a reasonable adjustments flag, the clinical record of interaction between staff and family.

### Staff interviews (2b)

Semi-structured interviews will be undertaken with clinical and non-clinical hospital staff working with children receiving cancer care. The only eligibility criteria is that staff have experience of providing care to children undergoing cancer treatment at the hospital research site. Interviews will take place within a private setting of the participant’s choosing, face to face or online using video conference calls. A topic guide will use flexible and open-ended questions to explore the participants’ experience of receiving or providing cancer care in relation to the study aims and will also be informed by concurrent study findings. Interviews will last approximately 60 minutes, as guided by the participant. The interviews will be recorded on an encrypted digital recorder and transcribed verbatim by a third-party transcription company. Sensitive interviewing techniques will be used due to the risk of causing emotional trauma in view of the topic. A standard operating procedure will be used to manage emotional distress. An ongoing reflective diary will be kept to account for situational context, non-verbal observations during interviews and to promote self-awareness during all data collection activities [51].

Data from Phase 2 will be curated and managed using qualitative data analysis software NVIVO 14. Data will be analysed by the research team using Braun and Clark’s reflexive thematic analysis [43]. Hence, the analytical approach will be inductive, beginning with immersion (active reading) of the data using paper and pencil. Initial open coding will be undertaken before more focused coding towards developing higher level themes or organising concepts. Data collection will continue alongside analysis, meaning that it will be possible to explore themes of interest concurrently. For example, early interview data will provide a framework for potential ‘lines of enquiry’ to observe how what is said to happen occurs naturalistically in practice. Selected excerpts of clinical encounters/interactions will also be explored using conversation analysis to support the overarching analysis [52].

### Phase 3 staff and family workshops

Face to face staff and family workshops will be planned following data synthesis of the first two work packages. Previous participants, staff and families, will be brought together to hear about the study findings and explore innovative solutions for improving experiences and equity of cancer care (3a) and co-design [53,54] outputs for the open access repository of information (3b). Workshops will be designed in conjunction with the PPI Groups and will be co-facilitated in an accessible way with the research team. All participants will be provided with information about the workshops and will be reimbursed for their travel and time.

### Ethics

The study has received ethical approval from the London – Camden & Kings Cross Research Ethics Committee and the Health Research Authority (Rec no. 24/LO/0410).

The main ethical considerations relate to the involvement of vulnerable children and young people. Using the team’s extensive experience in this field, we will take a multifaceted approach to safeguard participants from harm according to beneficence principles. In accordance with the Nuffield Council on bioethics, an individualised approach will be taken to obtaining informed assent/consent with all children and young people according to age, learning and communication needs in partnership with their parents. For those with learning disabilities, adjustments will be made around assent/consent processes to support understanding and information retention. Information will be provided according to their preference; multiple options have been developed including resources that combine words, pictures and symbols, also a Stop Motion Animation using Playmobil, to explain what their participation will involve. We will be cognisant of how children and young people may express a wish to withdraw from the study and how to navigate the end of the research relationship. Consent processes involving adult participants (staff and parents) will follow a similar ethical code.

Ethnographic case studies require special consideration around maintaining participant confidentiality. Some families may feel that observation is too intrusive at some points. The child or young person and parents will be reminded throughout the study that they can ask the researcher to leave at any point and will ensure they know how they can easily indicate this (e.g., using signs). The researcher will remain vigilant to signs of participants’ distress/discomfort during research encounters and will proactively manage these situations with minimal disruption to all those involved. Partnership and rapport with families will be critical and the researcher’s awareness of each individual’s right to privacy and dignity during observation. The researcher will follow up with families and health professionals after any encounters in which the researcher was asked to leave, to determine whether support can be offered.

Preventing staff knowledge of family participation is impossible where data collection occurs on a ward, strict anonymisation procedures will be followed to ensure data confidentiality. Photographs and audio make an invaluable contribution to ethnography, but it is recognised that this element of the study must follow strict consenting and data protection procedures. Any photos or audio will be deleted or destroyed that inadvertently breach confidentiality or anonymity of others without their permission. All electronic data from patient records will be deidentified before extraction. Upon publication of findings, we will not report information that might compromise site or individual identity, for example relating to rare diagnoses or treatment, or location.

Throughout the project, all investigators will manage collection, storage, processing and disclosure of personal information in alignment with GDPR (2016) and Data Protection Act (2018) legislation. Unique identification numbers will be given to all participants, made known only to the research team. Demographic data will be kept to a minimum and will be stored separately to confidential and anonymised research data within a restricted access network drive, under a restricted access folder for the core research team.

